### Qualitative interviews

Qualitative data will be collected as part of a concurrent embedded strategy [40]. Interview themes will include an exploration of experiences of recruitment, participation, LTAD/LVP and end-of-life care; beliefs about the role and value of the LTAD in refractory ascites; and practical steps and barriers involved in undertaking the LTAD.

Twenty-eight optional interviews (with 20 participants and 8 clinical key informants) will be undertaken by a qualitative researcher, with additional support if needed. Clinicians and research participants will be identified and recruited via the research team member. Patient recruitment will seek to reach a maximum diversity sample of participants, i.e. interview participants with a wide range of demographic characteristics, with purposive sampling (if feasible), informed by the IPOS (given that the individuals of this cohort are living with deteriorating health). The research team member will invite patients to participate in the qualitative interview study and will seek permission to pass contact details (normally telephone number) to the qualitative researcher. The qualitative researcher will contact participants to arrange a convenient time for the interview. As life expectancy in refractory ascites due to ESLD is on average 6 months, the qualitative interview methodology seeks to explore a wide range of patient experiences, recognising that participant beliefs and experiences may change across this period. Interviews will, therefore, be divided into two phases:*Phase 1* (weeks 0–8) 12 patients (6 from each arm), 4 clinical staff*Phase 2* (weeks 9–12) 8 patients (4 from each arm), 4 clinical staff

In the event of inability to recruit new participants for Phase 2 interviews, additional participants or repeat interviews will be sought during Phase 1. Interviews with key clinical staff will follow the same aims of patient interviews and will be anonymous (i.e. key informants will be asked to withhold patient identities).

Interviews will take place at participants’ homes or by telephone according to participant preference and geographical location. Clinical staff will be interviewed at their place of work or at a mutually convenient venue. Consent will be taken from all participants, including any carer requested by the participant to be present. For telephone interviews, consent will be taken verbally and recording will be started before telephone consent is taken, so that the verbal consent can be recorded as a separate file from the interview. Signed consent forms will be kept for 5 years. Interview data will be transcribed and the audio version deleted. The anonymised transcription of the interview (including the verbal consent) will be stored (labelled with patient study number).

To reduce participant burden, breaks will be allowed during the interviews if requested by the participants, and interviews will last between 20 and 60 min.

### Safety monitoring

A monitoring plan will be put in place and adhered to for each research site (see Additional file 2). Monitoring visits will be undertaken by the Brighton and Sussex Clinical Trials Unit (BSCTU) on behalf of the Study Sponsor. The study may be audited in line with the BSCTU or by the Sponsor requirements. Audits will be conducted by personnel independent from the research team.

Common Terminology Criteria for Adverse Events (AEs) (CTCAE, version 4.03) [41] will be used when assessing AE and serious adverse events (SAEs). As this is a feasibility study, all AEs and SAEs will be recorded in the source data and reported on the eCRF. Crucially, only those SAEs that in the opinion of the CI are related to the study intervention (LTAD) will be reported in an expedited manner to the BSCTU.

This feasibility RCT is investigating the LTAD in a cohort with ESLD. By its very nature, this is a group with high morbidity and mortality. Hence, in this patient population, worsening of existing conditions, hospitalisations, acute illnesses and deaths are expected. These events will be recorded in the eCRF but will not be reported to the BSCTU or the REC.

Expected/unexpected unrelated AEs/SAEs will include but not be limited to:Hepatic encephalopathyGastrointestinal bleeding related to peptic ulceration, hypertensive portal gastropathy or varicesLiver cancer and or its treatmentComplications of gastroscopy (perforation, bleeding)Complications of LVP (circulatory and or electrolyte disturbances, bleeding, bowel perforation, failed drainage)Complications of drug treatment for cirrhosis (lactulose, beta blockers, terlipressin, antibiotics, diuretics)Death related to the liver disease; will include death from liver failure, multiorgan failure, variceal bleeding and sepsis

### Expected serious adverse reactions (SARs)

If in the CI’s opinion a SAR is considered directly related to the LTAD and is an expected SAR, then this will be recorded on the eCRF and reported to the BSCTU immediately following the Safety Reporting SOP. Expected SARs will include the following (but only if they result in hospitalisation):Failure of LTAD insertionDrain leakage or blockageCellulitisBleedingPain at site of insertion not controlled by analgesiaSpontaneous bacterial peritonitisSepsis which in the opinion of the CI is directly related to the LTADDeath which in the opinion of the CI is directly related to the LTAD

### Suspected unexpected, serious adverse reactions (SUSARs)

This category will include all SARs that in the opinion of the CI are directly related to the intervention and are not listed as a known (expected) SAR. All SUSARs that occur between insertion of the LTAD and 3 months post insertion or death, whichever is earlier, will be recorded on the eCRF and emailed/faxed to the BSCTU immediately, at least within 24 h of the research team becoming aware in accordance with the BSCTU Safety Reporting SOP. The REC will be notified of any SUSAR to the study intervention by the BSCTU. For each SUSAR, all relevant information will be collected, and the SUSAR will be followed up until resolved or a final outcome reached.

The CI will have direct and ultimate responsibility for reviewing all reported SARs and SUSARs and will ensure that the BSCTU reports these appropriately according to the BSUH SOP on Safety Reporting in Non-Clinical Trial of an Investigational Medicinal Product (CTIMP) studies.

### Data analysis

#### Statistical analysis

Guidelines for feasibility studies suggest that analysing 12 participants in each arm will provide an adequate sample size with which to achieve our objectives [42]. However, since this is a cohort with a poor prognosis, attrition is likely to be high. In our pilot study of seven patients [26], survival post insertion ranged from 6 to 96 days (though the LTADs were inserted late in the disease trajectory). Due to the advanced disease stage of the participants, we are assuming a 50% attrition. The sample size will therefore be increased to 24 participants in each arm, i.e. a total recruitment target of 48 participants. This sample size will be adequate to inform the research methods for a definitive phase 3 RCT.

Recruitment rate will be evaluated in terms of the proportion of eligible patients who provide informed consent. Attrition at all stages will be recorded, particularly due to unwillingness or inability to manage the LTAD, as this is an indication of acceptability. Data will be analysed on available cases in the groups to which they were randomised. We will present these data as a flow chart. The amount of missing data will be summarised for each variable, but there will be no imputation. As this is a feasibility study, stopping rules will not be defined.

The flow of patients through the trial is depicted in the Consolidated Standards of Reporting Trials (CONSORT) diagram (Fig. 4) [43].

**Fig. 4 Fig4:**
[figure not shown]
Consort flow chart

Descriptive statistics will be used to summarise and compare the quantitative outcome measures to include (1) complication rates: failed insertion, drain leakage or blockage, cellulitis, bleeding, pain at site of insertion not controlled by analgesia, peritonitis, sepsis and death (the latter two only if directly related to the LTAD), (2) symptoms: IPOS, QOL (SF-LDQOL, EQ-5D-5 L) [28, 33–35] and (3) carer burden [36, 37] for each arm. Means and standard deviations will be determined for normally distributed outcomes and medians and interquartile ranges for skewed outcomes at the different time points and at the end of the study. Analyses will use all available cases following intention-to-treat principles. We will calculate 95% confidence intervals for parameter estimates as appropriate. Prior to the analysis of the data, a detailed statistical analysis plan will be written and signed off.

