#### Qualitative data analysis

If purposive sampling is not feasible, the proportion of participants choosing to participate in qualitative interviews will be noted. Interviews will be audio recorded and labelled using the same anonymous study number as the intervention component of this study. The same number will be used so that in the event of a participant reporting a serious concern about his/her condition or care, the qualitative researcher can raise this concern with the patient’s clinician. In this unlikely event, the researcher will inform the patient of the need to convey this information to the clinician. The qualitative researcher will have access to the clinical study data of the individual if needed.

Thematic analysis supported by qualitative software (NVivo) [45] will be used to extract overarching themes from the interviews to capture patients’ experiences and beliefs. Utilising the process of triangulation [46], the findings of the qualitative arm will be used to inform the quantitative results, particularly in the context of QOL and experience of end-of-life care provision.

Data will be analysed in a blinded manner. However, the research team members collecting information from the patients will always be aware of their allocation since a high level of scrutiny is necessary to ensure that there are no safety events in the LTAD group. Our service users were also insistent that participants not engage with multiple members of the research team, further excluding blinded data collection.

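### Sepsis and death enter the by-arm complication rates only if attributed to the LTAD, so these two outcomes cannot be compared between arms; LVP-specific complications are left off the list

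*Protocol article*

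**What the plan says.** In the Statistical analysis section of the protocol article (the paragraph after the Fig. 4 caption), the plan reads "Descriptive statistics will be used to summarise and compare the quantitative outcome measures to include (1) complication rates", to be given for each arm on available cases by intention to treat. Eight complications are listed. The last three carry this wording: "peritonitis, sepsis and death (the latter two only if directly related to the LTAD".

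The section on expected serious adverse reactions leaves it to the chief investigator's opinion whether sepsis or a death is directly related to the LTAD. That list is introduced with "Expected SARs will include the following (but only if they result in hospitalisation". On blinding, the Qualitative data analysis section says that "the research team members collecting information from the patients will always be aware of their allocation".

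The Safety monitoring section has a list of events classed as unrelated. It includes "Complications of LVP (circulatory and or electrolyte disturbances, bleeding, bowel perforation, failed drainage" and "Death related to the liver disease; will include death from liver failure, multiorgan failure, variceal bleeding and sepsis". The same section says that "all AEs and SAEs will be recorded in the source data and reported on the eCRF".

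**The concern.** A complication rate that is compared between randomised arms needs a definition that a patient in either arm can meet. For sepsis and death, the definition depends on the device received. One arm is fixed at zero. The other is fixed by a causal judgement that can be made only with knowledge of the treatment. The result is neither a comparison of how often patients in each arm become septic or die, nor a comparison of procedure harm, because LVP's own procedure harms are mostly not listed.

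This matters because the Background names bleeding and infection as the reasons LTADs have not been assessed in end-stage liver disease, and Outcome measures lists complication rates among the objectives. A definitive trial would be designed partly from these figures. Sepsis is the item most exposed: deaths appear elsewhere as attrition, but sepsis from any cause has no other stated by-arm summary.

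**Working it through.** **1. The plan's own figure.** The sample size paragraph starts from "analysing 12 participants in each arm will provide an adequate sample size" and allows for 50% attrition: 12 / (1 − 0.50) = 24 per arm, and 2 × 24 = 48. This reproduces exactly, and the point does not change it.

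**2. Where the list comes from.** Set beside the expected LTAD reactions, the eight complications in the analysis section match item for item and in the same order: failed insertion, leakage or blockage, cellulitis, bleeding, site pain, peritonitis, sepsis, death. An LTAD reaction list is therefore serving as a two-arm outcome. Of the LVP complications named under Safety monitoring, only bleeding is in it. Circulatory or electrolyte disturbance, perforation of the bowel and failure to drain are absent.

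**3. Which items are filtered.** The LTAD-related condition is attached to sepsis and death only. Peritonitis, bleeding and cellulitis have no such condition and can be counted in both arms.

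**4. Size of the filter for death.** Inputs: 24 per arm; 12 weeks of follow-up (Randomisation section); median survival of 6 months or less (Background). Assumption: exponential survival from randomisation, with the median varied below 26 weeks. Risk by week 12 is p = 1 − 0.5^(12/median).

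| Assumed median (weeks) | p at 12 weeks | Expected deaths of 24 | Counted in LVP arm |
|---|---|---|---|
| 26 | 27.4% | 6.6 | 0 |
| 20 | 34.0% | 8.2 | 0 |
| 12 | 50.0% | 12.0 | 0 |

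The last row equals the plan's 50% attrition if all of it were death. Even at the lowest risk, the chance of at least one death among 24 is 1 − (1 − 0.274)^24 = 0.9995. The planned definition would nonetheless report 0/24 for LVP, with an exact 95% interval of 0 to 14.2%, which would describe the definition and not the patients.

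**5. Effect on the difference.** Let f be the share of LTAD-arm deaths attributed to the drain (assumed 0 to 50%; the article gives no figure). The counted difference, LTAD minus LVP, is p_LTAD × f − 0.

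- Equal true risk of 27.4%: true difference 0; counted difference 0 to 0.274 × 0.5 = 13.7 points.
- LTAD 27.4%, LVP 40% (illustrative): true difference −12.6 points; counted difference 0 to +13.7.
- LTAD 40%, LVP 27.4% (illustrative): true difference +12.6 points; counted difference 0 to 0.40 × 0.5 = +20.0.

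The counted difference does not involve the LVP risk at all and can never fall below zero. It can overstate LTAD harm, or hide it if f is small. The same algebra applies to sepsis, for which the article gives no rate, so no size is put on it.

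**6. Hospitalisation condition.** Read literally, the expected-reaction list admits an LTAD-related death only if it led to hospitalisation. Safety monitoring requires expedited reporting of LTAD-related SAEs without that condition. The SUSAR section covers related serious reactions that are not on the expected list. Which category an LTAD-related death at home falls into is not stated plainly.

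**The case against.** A reader might infer that the whole safety comparison is a structural zero. The text does not support that: peritonitis and bleeding, both named as concerns in the Background, are unfiltered, as is cellulitis. The success criterion on LTAD removal does not use the filter either.

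A reader might also infer that bleeding after LVP, or peritonitis managed at home, is excluded from the rates because of the unrelated list or the hospitalisation condition. Those are safety-reporting categories, and the analysis section imports neither. Nor is there a contradiction in classing a septic death from liver disease as unrelated, since LTAD-related sepsis and death have their own entries.

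Nothing is irrecoverable. All events reach the eCRF, attrition due to death is a stated objective and is shown in the flow chart, and an independent committee monitors adverse events. A related death at home can be read as escalated under the SUSAR section. The trial is a descriptive feasibility study without a safety test, and all-cause event tables are ordinary content for the analysis plan, which is not shown.

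All of this stands, and it narrows the point. It does not remove it. The restriction on sepsis and death is a rule the article states, not a detail it leaves open, and it is attached to rates that are to be compared by arm. The planned blinded analysis does not help, because attribution happens before analysis.

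**Conclusion.** The point holds for sepsis and death. For these two outcomes the LVP arm is zero by definition, barring an LVP patient who receives an LTAD, and the LTAD count is one investigator's attribution in an open trial. They cannot be compared by randomised arm as written. The list is also asymmetric in omitting three of the four kinds of LVP complication that the article itself names.

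The deaths outside the LVP count number roughly 7 to 12 of 24 under the assumed exponential survival with a median of 26 down to 12 weeks. They are missing from the complication comparison only, not from the trial record. The spurious difference of up to 13.7 points at equal 27.4% risk rests on the assumed attribution range of 0 to 50%. For sepsis the gap is real, since no stated analysis compares all-cause sepsis by arm, but its size cannot be given from the article.

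This is a correction to an outcome definition. It does not undermine the design or the sample size of 48. The unclear category of an LTAD-related death outside hospital is a secondary point that needs reconciling; it is not evidence that such deaths go unreported.

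**What to change.** 1. In the Statistical analysis section, drop the LTAD-related condition from sepsis and death. Tabulate all sepsis and all-cause death by randomised arm over the 12-week follow-up, with LTAD-relatedness as a secondary column.
2. Add the LVP procedure complications from Safety monitoring that are missing from the list (circulatory or electrolyte disturbance, bowel perforation, failed drainage), so that complications of both randomised procedures are defined and counted symmetrically.
3. Reconcile the hospitalisation condition on expected reactions with the Safety monitoring and SUSAR sections, so that the category of an LTAD-related death outside hospital is clear.

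The events are already recorded on the eCRF. The cost is revised wording and one extra table; the target of 48 is unchanged.

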#### Health economics data analysis

The economic analysis will adopt the perspectives of the health and social care systems.

Using the patient-level database assembled from participant self-report and hospital and community nursing records, the feasibility study will identify the main resource items for which comprehensive data collection would be required in the main trial. Interactions between ascites management and other palliative care services will be explored. In particular, community nurse visits in both groups will be monitored, so *extra* visits required for the LTAD, compared to normal care, which was a major source of uncertainty in the earlier modelling study, can be identified [13]. The group mean total costs of services used in ascites management will be compared between LTAD and LVP.

The properties of the main clinical outcomes (IPOS, SF-LDQOL, EQ-5D-5 L) [28, 33–35] and the number of hospital days will be investigated to assess their value as measures of effectiveness for the definitive trial so that a primary outcome can be determined. Data on QALYs from EQ-5D-5 L [35] will be investigated for possible use in the economic evaluation. A preliminary cost-effectiveness analysis will be undertaken to determine the likely advantage of conducting a full trial [44]. A sensitivity analysis will be performed by varying the key cost drivers, such as the number of inpatient days and the cost of bed days.

#### Qualitative data analysis

If purposive sampling is not feasible, the proportion of participants choosing to participate in qualitative interviews will be noted. Interviews will be audio recorded and labelled using the same anonymous study number as the intervention component of this study. The same number will be used so that in the event of a participant reporting a serious concern about his/her condition or care, the qualitative researcher can raise this concern with the patient’s clinician. In this unlikely event, the researcher will inform the patient of the need to convey this information to the clinician. The qualitative researcher will have access to the clinical study data of the individual if needed.

Thematic analysis supported by qualitative software (NVivo) [45] will be used to extract overarching themes from the interviews to capture patients’ experiences and beliefs. Utilising the process of triangulation [46], the findings of the qualitative arm will be used to inform the quantitative results, particularly in the context of QOL and experience of end-of-life care provision.

Data will be analysed in a blinded manner. However, the research team members collecting information from the patients will always be aware of their allocation since a high level of scrutiny is necessary to ensure that there are no safety events in the LTAD group. Our service users were also insistent that participants not engage with multiple members of the research team, further excluding blinded data collection.

### Ancillary and post-trial care

At the end of the trial, participants will continue to be assessed by their usual medical care team. Those allocated to the LTAD arm will have the option, if they so wish, to continue with the LTAD under care of their usual consultant gastroenterologist/hepatologist.

#### Data Safety Monitoring Committee (DSMC)

The DSMC will be an independent committee chaired by [name] (Professor of Hepatology, Nottingham University NHS trust) with two other independent members, [name] (Chair of Medical Ethics at BSMS) and [name] (Professor in Infectious Diseases, BSMS and Hon Consultant, BSUHT), as well as at least one service user member. A study data report will be provided to the DSMC by the trial manager every 10–12 months for the first 2 years and then every 6 months for the last year, in accordance with the Terms of Reference for the Committee. The DSMC will meet as above to address any safety concerns, review any ethical issues raised and monitor adverse events. The DSMC will make recommendations to the TMG as appropriate and has the power to stop the trial if necessary. The DSMC will be independent of the Study Sponsor. Details of the Independent Data Monitoring Committee (IDMC) charter can be obtained from [contact].

## Discussion

The impetus for the REduced Drainage Utreatable Cirrhosis (REDUCe) trial was driven by our concerns that patients with ESLD receive suboptimal end-of-life care compared to those with other terminal conditions. Most individuals with ESLD almost always die in hospital [6] while receiving end-of-life care, even though in many cases palliative care provided within the community would be more appropriate and compassionate. Such an option is often not feasible due to the complex end-of-life needs of patients with ESLD (including LVP) and the fluctuating disease trajectory making it difficult to define when a palliative phase has been reached [6, 47]. Most patients with ESLD develop ascites [2, 3], and the management strategy in ESLD is thus often dictated by this specific symptom. Our own data suggest that approximately 40% of patients with ascites requiring LVP can go on to develop refractory ascites [48]. This condition has a major impact on the QOL in ESLD, due to factors such as direct physical discomfort but also the need for recurrent hospitalisation for LVP [3, 49]. We would argue that for many such individuals these recurrent hospitalisations impair their QOL. A more appropriate option would be to focus on holistic palliative care in the community, based on discussions on future wishes [49, 50]. This will require a multidisciplinary approach to the disease, reflected in the composition of the REDUCe study team.

Consistent with the lack of research in this complex cohort of individuals and therefore not unexpectedly, recruitment to this trial has been challenging. We found that clinicians who were not part of the study team were often reluctant, particularly in younger patients, to diagnose ESLD and discuss the implications of a limited life expectancy and purely palliative management. In some instances prospective participants were only identified late and unfortunately died before they could make an informed decision about trial participation. The patients themselves are often vulnerable and (in their opinion) disenfranchised and stigmatised. Finally, setting up new sites for a study that spans both acute hospital and community settings, often without existing research collaborations, has been difficult and time-consuming.

Conversely, we have already begun to note positive changes in attitudes, beliefs and practice of HCP locally and in the study sites. Simply by attempting to discuss the REDUCe trial, we have seen a change in attitudes towards symptom control and QOL as well as timely referral to palliative care. There is also increasing recognition that patients should be able to be more involved in decisions about their end-of-life care. This trial has raised the local profile of these under-researched patients, with wider recognition of the need for MDT communication and collaboration. Specifically, many local hospitals now discuss all patients with ESLD at a weekly liver MDM so as to identify in a timely manner those who are entering the palliative phase of their disease. This has undoubtedly driven the improvement in recruitment. The National Institute for Health Research (NIHR), acknowledging this and the potential of this study to result in a paradigm shift in end-of-life care in ESLD, has granted a funded extension for a year.

